## Abstract

**Background:**

Patient education is a crucial strategy for promoting prevention and diabetes self-management since glycemic control achievement involves taking medications, medical nutrition therapy, physical exercise, and behavior changes. However, patient education programs are still barely implemented in low- and middle-income countries. This trial aims to investigate whether a lifestyle education intervention added to physical exercising is superior to sole physical exercising regarding functional capacity, disease-related knowledge, health behaviors, cardiometabolic health parameters, quality of life, depression, and diet quality in individuals with prediabetes or diabetes.

**Methods:**

Multicenter double-blinded randomized controlled trial with two parallel arms involving 12-week intervention and 6-month follow-up. The eligible individuals (≥ 18 years, living with prediabetes or diabetes, literate, no clinical decompensation and/or physical and/or mental limitations that contraindicate physical exercising, written physician permission for exercise, no cognitive impairment, no vision limitations for reading, no confirmed diagnosis of unstable coronary disease or heart failure, no pacemaker and/or implantable cardioverter-defibrillator, no complex ventricular arrhythmias, no intermittent claudication, no recent cardiovascular event or cardiac surgery, and no currently enrolled in a structured exercise program) were recruited from two Brazilian cities and randomized to either (1) an Exercise and Lifestyle Education Program (ExLE) or (2) an Exercise Program (Ex), which can be delivered on-site or remotely based on the participants’ internet access and technology literacy. The primary outcomes will be changes in functional capacity and disease-related knowledge. The secondary outcomes will involve changes in health behaviors (health literacy, physical activity level, exercise self-efficacy, and medication adherence) and cardiometabolic health parameters (glycemic control, anthropometric measures, and cardiac autonomic control). Program adherence, satisfaction with the program, diabetes-related morbidity, and changes in quality of life, depression, and diet quality will be the tertiary outcomes. Assessments will occur at baseline, post-intervention, and after 6-month follow-up.

**Discussion:**

If superior effectiveness of ExLE compared to Ex program to improve the outcomes measures is found, this program could be delivered broadly in the Brazilian health system, especially in the primary care facilities where most individuals living with prediabetes and diabetes in our country are assisted.

**Trial registration:**

ClinicalTrials.gov, NCT03914924. Registered on April 16, 2019.

**Supplementary Information:**

The online version contains supplementary material available at 10.1186/s13063-024-08535-6.

## Administrative information

Note: the numbers in curly brackets in this protocol refer to SPIRIT checklist item numbers. The order of the items has been modified to group similar items (see http://www.equator-network.org/reporting-guidelines/spirit-2013-statement-defining-standard-protocol-items-for-clinical-trials/).

Role of sponsor {5c}	The study sponsor, acting as the initiating study site, has overseen the study design, data collection, management, analysis, and interpretation of data. The preparation of the manuscript and the decision to submit it for publication were made by the sponsor. It is important to note that the funders played no role or had any authority in the study design, data collection, management, analysis, or interpretation of data. Furthermore, they will not be involved in the writing of associated publications or in the decision-making process regarding paper submission for publication.

## Introduction

### Background and rationale {6a}

While the global prevalence of diabetes continues to rise, there are indications that some high-income countries (HIC) are experiencing a stabilization or even a decline in new cases [1]. This trend is likely attributable to effective preventive measures and comprehensive public health education programs [2]. In contrast, diabetes rates among adults in Brazil are on a steady upward trajectory [3]. Additionally, the incidence of prediabetes is showing a marked increase on a global scale [4]. This contrast underscores the critical importance of sustained efforts in public health strategies tailored to different socioeconomic contexts.

The functional capacity and cardiac autonomic control are impaired in patients with diabetes [5, 6], and the former is related to poor prognosis due to increased cardiac risk and mortality [7, 8]. The mechanisms that explain the impact of diabetes on functional capacity are not completely known [6, 9]. The harmful effects of hyperglycemia on muscle strength and resistance, as well as other factors such as impaired glucose metabolism, long-term complications, and comorbidities, could contribute to the reduction of functional capacity in patients with diabetes [6, 9, 10]. Therefore, diabetes requires continuous and comprehensive medical care to prevent and manage its acute and long-term complications, which may affect the quality of life and patients’ daily physical capacity [11]. Diabetes treatment involves the use of medications and lifestyle modifications, including self-management education and support, medical nutrition therapy, and physical exercise to achieve glycemic control [12].

Although it is well known that physical exercise contributes to blood glucose control and the reduction of cardiovascular risk factors [11, 12], compliance remains a challenge. It demands overcoming several barriers to engage in a healthy lifestyle, such as being active [13]. According to data from the Surveillance System of Risk and Protection Factors for Chronic Diseases by Telephone Survey, adults with diabetes in Brazil do not get enough physical activity [14].

In this context, patient education is a fundamental component of diabetes care due to the effectiveness of educational interventions in promoting lifestyle change [12, 15], and the positive association between disease-related knowledge, treatment adherence, and a healthy lifestyle [16, 18]. Although diabetes guidelines recommend patient education as a component of diabetes care [12, 19], educational interventions for individuals living with or at risk of this condition have been scantly investigated in low- and middle-income countries (LMIC) such as Brazil [20, 21]. The impact of patient education on behavior change has not been frequently considered in these settings, with most studies on this topic being carried out in high-income countries [17, 22, 23]. Additionally, there is a lower adherence to self-care behaviors by patients with diabetes in LMIC compared to their peers in HIC which could be explained by the limited access to healthcare services [24].

A patient education program tailored to Brazilians living with diabetes and prediabetes was developed [25] drawing from the Diabetes College curriculum. Originally developed in English as part of the Diabetes Program at the Toronto Rehabilitation Institute in Canada, this curriculum has been validated by prior studies showing significant improvements in disease-related knowledge [26, 27], physical activity [26, 27], food intake [26, 27], exercise self-efficacy [26], and health literacy [26]. Given that physical exercise is recommended by the Brazilian guidelines to prevent and treat diabetes [28, 29], the patient education program for Brazilians was combined with an exercise program (Exercise and Lifestyle Education Program) to investigate whether patient education can promote better outcomes than physical exercise alone.

The feasibility, acceptability, and initial efficacy of the Exercise and Lifestyle Education Program were evaluated through a randomized pilot trial [30]. Additionally, its feasibility for remote delivery in an internet-based format was demonstrated [31]. Drawing from the results of the randomized pilot trial [30], we hypothesize that the Exercise and Lifestyle Education Program will yield significantly superior outcomes compared to exercise alone for individuals with prediabetes and diabetes in our setting.

### Objectives {7}

The purpose of this multicenter randomized controlled trial is to pragmatically investigate the effects of an Exercise and Lifestyle Education (ExLE) program compared to an Exercise Program (Ex) on functional capacity, disease-related knowledge, health behavior, and cardiometabolic health parameters in individuals with prediabetes and diabetes living in Brazil. Furthermore, program adherence, satisfaction with the program, quality of life, depression, diet quality, and 6-month related diabetes morbidity will also be investigated.

### Trial design {8}

This is a double-blinded (both outcomes’ assessors and data analysts) multicenter randomized controlled trial featuring two-arm parallel groups over 9 months (comprising a 12-week intervention period followed by a 6-month follow-up) with a 1:1 allocation ratio that follows the SPIRIT reporting guidelines [32].

## Methods: participants, interventions, and outcomes

### Study setting {9}

This study will be conducted in Juiz de Fora and Belo Horizonte, two cities in Minas Gerais, a southeastern Brazil’s state. Belo Horizonte, the state capital and largest city, is located in its Central Region, while Juiz de Fora, although medium-sized, holds the distinction of being the largest city in the Mata Region of Minas Gerais.

### Eligibility criteria {10}

Individuals from both sexes were eligible to participate in the study if they met all the following inclusion criteria and did not meet any exclusion criteria (Table 1).

**Table 1 Tab1:** Inclusion and exclusion criteria

Inclusion criteria	
Age	≥ 18 years old
Current history of prediabetes or diabetes	Self-reported
Literate	Able to understand, read, and write a short simple statement on his/her everyday life
Written physician permission for exercising	Signed by the participant’s doctor
No cognitive impairment	Six-item screening scoring ≤ 4
No vision limitations for reading	
No confirmed diagnosis of unstable coronary artery disease or heart failure	
No pacemaker and/or implantable cardioverter defibrillator	
No recent cardiovascular event or cardiac surgery	≤ 6 months
No intermittent claudication	
No currently enrolled in a structured physical exercise program that follows diabetes guidelines	Accumulating 150 min per week of aerobic exercise and perform muscle-strengthening exercises two to three times per week
Exclusion criteria	
Clinical decompensation that contraindicates physical exercising	
Physical limitations	Any physical limitation that prevented the participant from engaging in the physical exercise
Mental limitation	Any limitation that prevented the participant to understand the educational content
Complex ventricular arrhythmias	Atrial flutter or atrial fibrillation, multiple atrial or ventricular ectopy, and atrioventricular or ventricular block

The potential trial participants were invited to self-respond to questions regarding inclusion criteria on a Google digital form. From the responses, those who seemed eligible were invited for the baseline assessment during which all the eligibility criteria were confirmed by the research team before starting the data collection. Cognitive impairment was assessed on-site by the six-item screener prior to collecting signatures on the informed consent form. The six-item screener is scored by a simple summation of errors, with individuals making more than two errors (i.e., scoring lower than four hits) identified as having cognitive impairment [33].

Participants who present cardiac electrical conduction or rhythm disturbances (e.g., atrial or ventricular ectopy and atrioventricular or ventricular block) or who have changes in cardiovascular medication prescription during the study will be excluded from cardiac autonomic control assessment.

### Informed consent {26a}

Research team members, previously trained in good clinical practices and about the study protocol, screened the eligibility of potential trial participants, enrolled those with confirmed eligibility, provided explanations of the study procedures, and collected signatures on the informed consent form from each participant.

### Additional consent provisions for collection and use of participant data and biological specimens {26b}

This trial will not collect biological specimens; therefore, biological specimens will not be stored or utilized for research purposes. All data collection procedures are outlined in the informed consent form.

## Interventions

### Explanation for the choice of comparators {6b}

Given the established evidence demonstrating the beneficial effects of physical exercise in managing blood glucose levels and reducing cardiovascular risk factors for individuals with diabetes [11, 12], as well as the national recommendations to exercise regularly to prevent and treat diabetes [28, 29], this study will employ an exercise intervention for the control group.

### Intervention description {11a}

The study interventions could be delivered on-site or remotely. Before randomization, the enrolled participants were screened for internet access and technology literacy using an instrument developed by the researchers based on best practices in digital health literacy [34] (see Additional file 1). Participants who answered “yes” to all questions were able to choose their preferred format for receiving the intervention. Those without internet access and/or limited technology literacy will receive the intervention on-site.

### Exercise Program

The Ex program was developed based on recommendations of the Brazilian Diabetes Society Guidelines [28, 29]. It will last 12 weeks and consist of aerobic exercise sessions designed to achieve a minimum of 150 min per week, with muscle-strengthening exercises incorporated two to three times per week starting from the fourth week of the intervention. Each exercise session will include warm-up (stretching), aerobic exercise (moderate-to-vigorous intensity walking according to the Borg Rating of Perceived Exertion exercise scale modified [35]), and muscle-strengthening using the own body weight and elastic bands (one-to-two sets of 10–12 repetitions of row, half-squat or leg extension, biceps curl, standing knee flexion, shoulder external rotation, heel raise, wall push up, lying down abdominal, elbow extension, and 15 s of plank).

For participants receiving the intervention on-site, 16 supervised 1-h exercise sessions will be delivered twice a week from the first 4 weeks and once a week from the fifth week onward. In addition, these participants will receive counseling to exercise in the community to accumulate 150 min per week of aerobic exercise and perform muscle-strengthening exercises 2 to 3 times per week.

Participants receiving the intervention remotely will first attend an on-site supervised exercise session to be instructed on the correct execution of aerobic and strengthening exercises to ensure proper performance. After this initial session, the exercise intervention will be delivered through a website specifically developed for the Ex program participants. Additionally, participants will receive weekly reminders about the exercise routine via WhatsApp messages from the research team.

Participants will receive guidance on recognizing signs and symptoms of effort intolerance and instructions on how to respond in such situations. They will be asked to record their weekly exercise routine and any exercise side effects in an exercise diary. Additionally, they will be encouraged to self-monitor their heart rate by taking their pulse before and after exercise. Participants who use insulin or secretagogue medications will be instructed to measure capillary blood glucose before and after exercise. Participants with hypertension will be counseled to measure blood pressure before exercise during the first two sessions or in subsequent sessions if symptoms suggestive of changing blood pressure levels are present.

### Exercise and Lifestyle Education Program

The ExLE program combines the Ex program with a patient education program tailored for Brazilians living with diabetes and prediabetes, with detailed descriptions available in a previously published study [25]. The ExLE will last 12 weeks and consist of the same procedures described for the Ex program plus eighteen education classes following the schedule of educational sessions for the Diabetes College program in Brazil [25].

For participants receiving the intervention on-site, 18 30-min education classes will be delivered twice a week during the first 4 weeks and once a week from the 5th week onward, before or after the supervised 1-h exercise sessions. Participants will receive a printed version of the Diabetes College patient guide [36].

Participants receiving the intervention remotely will first attend an on-site supervised exercise session to be instructed on aerobic and strengthening exercises exertion and ensure proper exercise execution. Additionally, they will receive orientation on navigating the ExLE program website to access and fill out exercise and study diaries, as well as access educational video lessons and other support materials. After this on-site session, both the exercise and patient education components of the program will be delivered through a website specific to ExLE program participants developed for this study.

The educational content will include:Eighteen educational video lessons: recorded by the research team, lasting approximately 20 min each, and based on the Diabetes College program in Brazil;Twelve videos related to weekly topics: THRiVE videos integrating chronic disease management and behavior change principles to help develop self-management skills through goal setting and action planning; and, A printed version of the Diabetes College patient guide [36].

Additionally, participants will receive weekly WhatsApp text messages from the research team to remind them about the exercise routine, materials in their lesson plan, and the importance of tracking access to educational content in the study diary.

### Criteria for discontinuing or modifying allocated interventions {11b}

Since study participation is voluntary, participants have the right to withdraw from the study at any time. Upon withdrawal, no further data will be collected from them, although any data previously collected will be preserved in accordance with the terms outlined in the informed consent form. It is important to note that once a participant withdraws from the study, they will not be permitted to re-enter at a later date.

### Strategies to improve adherence to interventions {11c}

In on-site delivery mode, participants who did not attend the intervention session for that week will receive a WhatsApp message from the research team to remind them of the scheduled intervention for the following week. In remote delivery mode, the research team will check participants’ exercise and/or study diary completion to assess their engagement in exercise and/or education lessons. Participants who show no engagement in exercise and/or educational lessons for that week will receive a WhatsApp message reminding them about the exercise and/or study routine.

### Relevant concomitant care permitted or prohibited during the trial {11d}

All participants will receive counseling on exercising in the community to achieve the recommended 150 min per week of aerobic exercise and perform muscle-strengthening exercises two to three times per week using elastic bands provided during the intervention. Besides walking, participants may choose alternative aerobic exercise modalities such as swimming, running, or biking to meet the aerobic exercise recommendations.

### Provisions for post-trial care {30}

No post-trial care provision will be offered, as no harm is anticipated from trial participation, and participants will not receive compensation.

### Outcomes {12}

#### Primary outcomes

The primary outcomes of this study will include functional capacity and disease-related knowledge. Functional capacity will be measured by the distance covered in meters during the incremental shuttle walk test (ISWT) [37], while disease-related knowledge will be assessed using the total score of the Brazilian Portuguese version of the DiAbeTes Education Questionnaire (DATE-Q) [38]. The DATE-Q total score, ranging from 0 (indicating no disease-related knowledge) to 20 (indicating the highest level of disease-related knowledge) is obtained by a 20-item questionnaire with response options of true/false/do-not-know. The primary outcomes will be measured during baseline and outcomes assessment appointments.

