### Sample size {14}

The sample size was calculated considering the ISWT distance as the primary outcome, using parameters derived from a previous study involving educational intervention in cardiac rehabilitation [50]. The calculation was performed using R Software version 3.4.3, with the following parameters: a moderate effect size (*d* = 0.20), 80% statistical power, a 5% alpha level, one-sided test, two arms, and three measurements. A total sample size of 200 participants (100 per arm) was determined. Assuming a 20% attrition rate, based on a previous study [50], 120 participants would be enrolled in each arm to ensure that 200 participants complete the study protocol.

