#### Primary and secondary outcomes

Primary and secondary outcomes will be presented as central tendency and dispersion measures. Data distribution will be analyzed using the Shapiro–Wilk test. The analysis of variance (2 × 2 ANOVA) will compare data between baseline and post-intervention and between groups. An alpha of 5% will be considered for statistical significance, and post hoc comparisons will be performed to detect two-by-two differences. In case of missing data, the statistical procedures will follow the intention to treat.

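### Two primary outcomes are tested at a flat 5% with no stated success rule, and the trial is sized on only one of them

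*Protocol article*

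**What the plan says.** Two places name two primary outcomes. The abstract (Methods) has "The primary outcomes will be changes in functional capacity and disease-related knowledge", and the section Primary outcomes has "The primary outcomes of this study will include functional capacity and disease-related knowledge". The latter defines them as ISWT distance in metres and the DATE-Q total score (0 to 20).

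The statistical section headed Primary and secondary outcomes gives one rule for both classes of outcome. On the model: "The analysis of variance (2 × 2 ANOVA) will compare data between baseline and post-intervention and between groups". On the level: "An alpha of 5% will be considered for statistical significance, and post hoc comparisons will be performed to detect two-by-two differences". It gives no split of alpha, no order of testing, and no statement that both primary outcomes must succeed or that one is enough.

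Sample size {14} works from a single outcome: "The sample size was calculated considering the ISWT distance as the primary outcome". DATE-Q does not enter that calculation.

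The abstract (Discussion) links the result to wide use without saying which outcome carries the claim: "If superior effectiveness of ExLE compared to Ex program to improve the outcomes measures is found, this program could be delivered broadly".

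**The concern.** With two primary outcomes, the plan has to say what counts as a positive trial, because the error rate and the power both depend on it. If either outcome is enough, two tests at 5% give more than a 5% chance of at least one false rejection. If both are needed, there is no inflation, but power is lower than for either outcome alone. The protocol does not choose between them.

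The choice also decides what the headline means. By the intervention descriptions, ExLE is the Ex program plus education classes, and DATE-Q measures disease-related knowledge. The background section reports that the source curriculum had already improved such knowledge in earlier studies. A gain on DATE-Q with no gain on ISWT is therefore a realistic result. Without a rule, it could be reported as a positive primary result and as superiority overall, although the outcome on which the trial was sized was negative.

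**Working it through.** **Inputs from the protocol.** Two primary outcomes; a 5% level; no interim analysis. Sizing: ISWT only, d = 0.20, 80% power, 5% one-sided, two arms, three measurements, 100 completers per arm. The correlation between the ISWT and DATE-Q test statistics is not given, so a range is assumed. One treatment comparison per outcome is counted.

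**1. The plan's own sample size.** With a single measurement, n per arm = 2(z₁₋α + z₁₋β)²/d².
- As stated (d = 0.20, one-sided): 2(1.645 + 0.842)²/0.20² gives 310 per arm, not 100. Power at 100 per arm is Φ(0.20·√50 − 1.645) = Φ(−0.231) = 40.9%.
- With d = 0.40, two-sided: 2(1.960 + 0.842)²/0.40² gives 99 per arm, 198 in total, which fits 200. This amounts to reading 0.20 as Cohen's f.
- Three measurements could also lead to 200 under an unstated correlation. For d = 0.20, one-sided, with the mean of two post-baseline values adjusted for baseline, the total is 224 at a within-person correlation of 0.7 and 162 at 0.8.

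The 200 therefore cannot be reproduced from the stated inputs, but it is not shown to be wrong. This matters here only because any power cost needs an assumed effect size.

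**2. Family-wise error if either outcome counts and both effects are null.**
- Independent tests: 1 − 0.95² = 0.0975. The bound by simple addition is 0.10.
- Correlated tests (bivariate normal):

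| Assumed correlation | Two-sided | One-sided |
|---|---|---|
| 0.2 | 9.64% | 9.48% |
| 0.5 | 9.07% | 8.78% |
| 0.7 | 8.35% | 8.04% |
| 0.9 | 7.04% | 6.81% |

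The two-sided figures count false rejections in either direction. The one-sided figures count only those in favour of ExLE. This is one reason why sidedness has to be settled.

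**3. If DATE-Q truly improves.** Only the ISWT hypothesis can then be falsely rejected, so the chance of a false primary rejection is 5%.

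**4. If both outcomes are required.** No adjustment is needed. With 80% power for each, joint power is 0.80² = 64% if the tests are independent. The 80% for DATE-Q is an illustration, since the protocol gives no sizing for it.

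**5. Effect of Holm's procedure.** The smaller p-value is compared with 2.5%; if it passes, the larger is compared with 5%. When both effects are null and the tests independent, the error is 1 − 0.975² = 4.94%. ISWT is tested at 2.5% only when DATE-Q is not rejected at 2.5%. In that case, with 100 per arm and a single measurement:

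| Assumed effect and side | ISWT power at 5% | ISWT power at 2.5% |
|---|---|---|
| d = 0.40, two-sided | Φ(2.828 − 1.960) = 80.7% | Φ(2.828 − 2.241) = 72.1% |
| d = 0.40, one-sided | 88.2% | 80.7% |
| d = 0.20, one-sided | 40.9% | 29.3% |

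**The case against.** The strongest reply has four parts.

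- **No either-outcome rule is stated.** A reader might infer that a win on one outcome is enough and conclude that the false-claim rate is in fact nearly doubled. The documents do not support that. The abstract speaks of improving the outcomes in the plural, and the hypothesis and objectives contain no win rule. This part stands: 9.75% is conditional on an either-outcome rule.
- **The two worries do not occur together.** The 9.75% needs education to have no effect on either outcome. If it truly raises knowledge, the error is 5%, and what remains is a question of how the result is labelled. This also stands. In that case Holm changes little, and the separate conclusions do the work.
- **A multiplicity rule may sit in an analysis plan that is not shown, and sizing on one of two primary outcomes is common.** Both are fair. But the protocol does more than stay silent. It fixes two primary outcomes, sets one 5% level for all outcomes, and elsewhere works with a single primary outcome. If an analysis plan already holds the rule, the remedy is to state it here.
- **If each outcome supports only its own claim, the need for adjustment is debated.** True, but the protocol does not limit its claims in that way.

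**Conclusion.** The point holds in conditional form. The protocol names two primary outcomes, sets 5% for each and sizes the trial on one, without defining success.

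The family-wise error is up to 9.75%, and about 7% to 9.6% for assumed correlations of 0.9 to 0.2. This applies only if either outcome counts and neither effect is real. If DATE-Q truly improves, the error on ISWT is 5%, and the risk is that a knowledge-only result is presented as overall superiority. If both outcomes were required, the issue would be power and not type I error.

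A reader might also take a fall in ISWT power from 80% to 72% as following from the protocol. It does not: it uses d = 0.40, two-sided, where Sample size {14} states d = 0.20, one-sided.

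This is a gap worth closing because it bears on the headline claim. It does not invalidate the trial.

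**What to change.** Before the analysis, add a short statement to the statistical section:

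- The two primary hypotheses (ISWT and DATE-Q) are tested with Holm's procedure at an overall 5%.
- The tests are declared one-sided or two-sided, and this is reconciled with the one-sided sizing in Sample size {14}.
- A separate conclusion is drawn for each outcome. Superior functional capacity is claimed only if the ISWT hypothesis is rejected.

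Sample size {14} should also say that ISWT is the one of the two primary outcomes used for sizing.

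**Cost.** This takes a few sentences and no new data. The smaller p-value must reach 2.5%. ISWT loses no power if DATE-Q is rejected first. Otherwise the loss depends on the effect size: from about 80% to 72% under the assumed d = 0.40, two-sided, 100 per arm, with the other assumed cases in the second table of the working.

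**Timing.** Trial status expects data collection to finish by December 2024 and closure in May 2025, after the analysis. No interim analysis is planned, and the analyst is blinded to allocation. On that schedule, the rule can be fixed before results are known. A rule chosen afterwards would carry little weight.
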